## Discussion

The overall aim of this research is to create and disseminate an intervention package for the self-management of PASC symptoms. This brief, cost-effective and scalable intervention can be available to any licensed therapist with mental health expertise and enable treatment of patients regardless of geographic location or mobility restrictions and will enable treatment without concern for infection risk to patients or therapist. The current RCT protocol will determine if the Education and Self-Management Strategies group offers better (or at least non-inferior) symptom management outcomes compared with the Mindfulness and waitlist groups. The inability to attribute many symptoms to a natural cause may be anxiety-provoking for patients, which emphasizes the importance of education to understand the range of possible non-specific and specific symptoms, and mindfulness for accepting symptoms non-judgementally/agnostically and destigmatizing discomfort by alleviating secondary maladaptive attributions.

The increasing strain of PASC on healthcare resources may deleteriously affect the management and care of other patient populations (38, 97). Literature on the challenges of self-managing symptoms of Long COVID is limited at this time, however we can learn from research on other chronic conditions (e.g., chronic obstructive pulmonary disease, rheumatic diseases, kidney disease) that likely present similar challenges and limitations that individuals may encounter in their recovery journey (80, 98–100). Firstly, the heterogeneity of symptoms and their unpredictable nature make it challenging to develop universally effective strategies. What works for one person may not necessarily benefit another due to the diverse manifestations of Long COVID. Additionally, the limited understanding of the underlying mechanisms and long-term effects poses a challenge in tailoring targeted interventions. The fluctuating and persistent nature of symptoms can also create difficulties in establishing a consistent and manageable routine. Furthermore, the emotional toll of prolonged illness, including anxiety and depression, can impact one’s ability to effectively self-manage (98, 99). Access to healthcare resources and professional guidance is another limitation, as not all individuals may have equal opportunities to consult with specialists or access tailored medical advice (98–100). The proposed intervention, which provides accessible, remotely delivered education and teaching strategies pertaining to the diverse symptom domains of Long COVID, was designed to mitigate some of these challenges.

Hence, the study stands to reduce the suffering and improve the quality of life of patients with PASC. Recognizing the unique and diverse nature of symptoms, the strategies and education intervention protocol incorporates a combination of educational modules, teaching of practical strategies, interactive question and answer period and peer support, to empower participants with knowledge, skills, and a robust support system. Educational presentations are tailored to provide insights into the varied symptoms and their management, fostering a proactive approach to healthcare. A question-and-answer period ensures that individuals receive guidance specific to their experiences, promoting a targeted and effective self-management strategy. Peer support, on the other hand, creates a community where shared experiences foster mutual understanding and encouragement. The ultimate goal is to enhance the overall quality of life for participants by mitigating symptom burden and intrusiveness, improving coping mechanisms, and fostering confidence to self-manage. We anticipate that a well-rounded approach to self-management will not only alleviate symptoms but also positively impact mental health, thereby contributing to an improved quality of life. Moreover, the intervention may also help to reduce the impact of PASC on the healthcare system by empowering participants to manage their condition independently and helping patients to discern when to seek out physician support for symptoms and when to self-manage. This, in turn, may alleviate the burden on healthcare resources while offering individuals a sense of control and agency over their health. Through these interventions, our study aspires to bridge existing gaps in Long COVID care and contribute meaningful insights to the broader field of chronic illness management.

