We will undertake a two-phase randomized controlled trial (RCT) to determine feasibility and effect size (Phase 1) and efficacy (Phase 2) for a novel 8-week Education and Self-Management Strategies group compared to a mindfulness skills program. Phase 2 is a full-scale quantitative-only RCT, with refinements and power analysis based on Phase 1 results, and an additional third no-treatment control arm. Outcomes of interest include confidence and ability to self-manage symptoms, quality of life, healthcare utilization. Hypotheses: Both interventions will be associated with enhanced mood, anxiety, quality of life and management of dyspnea symptoms. The education and self-management strategies program will additionally increase confidence to self-manage symptoms, decrease intrusiveness of Long-COVID symptoms in everyday life, and decrease medical visits, more so than the mindfulness group.

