### Study design

The Phase 1 trial is a block randomized, controlled, parallel group, two arm, assessor-blinded trial with a 1:1 allocation. Participants will be randomly assigned to either the Education and Self-Management Strategies or the Mindfulness Skills groups. The allocation sequence is determined using the random function in Microsoft Excel by the study coordinators prior to recruitment. The study coordinators will screen, consent, enroll, and assign participants to their study identity numbers. Qualitative assessment of *N* = 20 patients from the Education and Self-Management group will be purposively (i.e., subjectively) sampled to attain a heterogeneous subset of patients. Qualitative information will be combined with quantitative to permit a more thorough understanding of the outcomes and to aid in further program refinement before undertaking the Phase 2 full-scale RCT. This study design is summarized in COSORT flow diagram presented in Figure 1.

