**Figure 1 fig1:**
[figure not shown]
CONSORT study flow diagram of the present protocol; CONSORT, Consolidated Standards of Reporting.

Phase 2 will be a full-scaled trial with an additional third arm (1:1:1 allocation) as a non-treatment, standard-of-care group, with refinements and power analysis based on Phase 1 results.

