#### Education and Self-Management group protocol

All 8 sessions include education and independently deployable practical strategies (e.g., energy conservation, mindfulness and Cognitive Behavioral Therapy) and principles of self-compassion; self-care, cued diaphragmatic breathing, and phased return to physical activity that will be practiced during and between sessions. While the literature reveals that PASC symptoms can have specific aetiologies, the diagnosis of the etiology of a given symptom in a given patient may be uncertain. Moreover, the presence of some PASC symptoms may cause or exacerbate other symptoms (e.g., fatigue may result in or worsen attentional difficulties). Therefore, the education and strategies we provide are intended to be useful whether or not we have certainty of the underlying symptom cause in any given patient. Restated, the focus is on providing education and strategies for ameliorating symptoms, without making any assumptions about the cause of symptoms in any individual patient.

Benefits of this type of protocol (i.e., strategies and education) include non-invasiveness and no financial cost to patients. This is important given growing concern that in the absence of treatment for the wide-ranging symptoms of PASC, pernicious treatments (80–83) may fill the void.

Each session will end with a question-and-answer period. The content presented in each week is outlined in Table 1. During weeks 3–6, medical experts will deliver a 20–25-min presentation on their respective area of expertise and its relationship to Long-COVID, and provide self-management strategies.

**Table 1 tab1:** Overview of Education and Self-Management Strategies group protocol content.

Week	Topic	Subject expert(s)
1	Overview & Introduction	Psychologist
2	Intro to self-management strategies: discuss the importance of self-care/self-management of symptoms in recovery (e.g., Goal Setting, Energy Conservation, Managing Fatigue, Activity Scheduling, Sleep and Exercise/Nutrition)	Psychologist
3	Respiratory symptoms: presentation on the topic of long-term respiratory symptoms associated with COVID, recommendation of at-home breathing strategies and exercises (e.g., diaphragmatic breathing, active cycle breathing), discussion and question and answer period	Respirologist & Physiotherapist

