#### Efficacy analyzes

To assess pre-to post-treatment and follow-up changes for the primary outcome (PMCSMS), we will undertake repeated measures group (Education vs. Mindfulness) by time (pre-, post-, and follow-up-education/mindfulness/waitlist group). ANCOVAs controlling for acute COVID-19 severity and time post-diagnosis. Secondary outcomes will also be examined in the same manner.

Hierarchical regression analyzes will be performed to examine impact of potential moderator variables on pre-to-post treatment improvement on the PMCSMS. In the first block, the moderators will be age, acute COVID severity, and time-post diagnosis. Sex and gender will be included in the second block, and Brief COPE, AIIR and MHLC will be added in the final block. Analyzes of repeated measures data will be performed using the Mixed Models for Repeated Measures (MMRM) methodology (96). We will employ a comparison of bias-corrected covariance estimators for MMRM analysis in longitudinal data with dropouts in order to accommodate the possibility of missing assessments or of assessments at different times post-diagnoses and to provide an effective framework for hierarchical regression analyzes and further exploratory analyzes (96).

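### The Discussion adds a non-inferiority aim that the printed hypotheses, test and Phase 1 sample size do not support, and the waitlist arm is not confined to Phase 2

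*Protocol article*

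**What the plan says.** All references are to the protocol article.

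- **Discussion.** The aim is put as a question with two acceptable answers, namely whether Education "offers better (or at least non-inferior) symptom management outcomes compared with the Mindfulness and waitlist groups". Non-inferiority is mentioned nowhere else.
- **Aims and hypotheses.** Both programmes are expected to help mood, anxiety, quality of life and dyspnea management. Education is expected in addition to raise confidence to self-manage and to "decrease intrusiveness of Long-COVID symptoms in everyday life, and decrease medical visits, more so than the mindfulness group". That is a superiority hypothesis, and it covers the construct measured by the primary outcome (PMCSMS).
- **Participants.** The Phase 1 size rests on paired tests from an earlier concussion study: effect size 0.59, 26 pairs, then allowances of 20% and a further 25% for loss, giving 45 per arm.
- **Study design.** Phase 1 has two arms: "Participants will be randomly assigned to either the Education and Self-Management Strategies or the Mindfulness Skills groups". Phase 2 adds a third arm "as a non-treatment, standard-of-care group", with its size left to a power analysis based on Phase 1.
- **Efficacy analyzes.** The model is "repeated measures group (Education vs. Mindfulness) by time (pre-, post-, and follow-up-education/mindfulness/waitlist group"), fitted as an ANCOVA, with MMRM for the repeated measures.
- **Education and Self-Management group protocol.** The Education arm itself teaches "independently deployable practical strategies (e.g., energy conservation, mindfulness and Cognitive Behavioral Therapy").
- **Ethics and dissemination.** A larger trial follows if preliminary efficacy is seen in Phase 1. Its control patients are treated after the control phase.

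**The concern.** A superiority test that fails to reach significance is not evidence of non-inferiority. That conclusion needs a margin fixed in advance and a confidence interval that excludes it. If the aim allows both answers but the design provides for only one, a non-significant Phase 1 result could later be described as at least non-inferior, with nothing in the protocol to test the description against.

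Three features would make such a reading weak:

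- By the Abstract's own account, neither type of intervention has yet been evaluated in PASC to the authors' knowledge. Mindfulness therefore has no established effect in this population from which to justify a margin.
- Education contains mindfulness content, which draws the two arms together.
- Against a waitlist or untreated group, being no worse shows no benefit at all.

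The waitlist wording is a separate, smaller problem. The analysis sentence fits neither phase. For Phase 1 there is no waitlist arm. For Phase 2 the group factor leaves out the third arm, and the waitlist appears inside the time factor instead.

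**Working it through.** **1. Reproduce the plan's own figure.** Inputs from Participants: effect 0.59 and 26 pairs. Standard alpha and beta are taken, as an assumption, to be two-sided 0.05 and 80% power. A paired t-test (noncentral t) needs 25 pairs, and 26 pairs give 82.4% power. Losses: 26/0.80 = 32.5, rounded up to 33; 33/0.75 = 44, against 45 stated. The size reproduces to within one pair and one patient per arm, but as a within-group calculation. It is not sized for a between-arm comparison of either kind.

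**2. Analysable numbers per arm.** No loss: 45. After 20%: 45 × 0.80 = 36. After a further 25%: 36 × 0.75 = 27 (1-month follow-up only).

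**3. Smallest margin Phase 1 could exclude.** The protocol states no margin, so the calculation is run in reverse. Assumptions: true difference 0, one-sided 0.025, 80% power, SD units. The normal approximation is margin = (1.96 + 0.84) × √(2/n). The two-sample t calculation is slightly larger. Adjusting for a baseline correlation ρ multiplies the margin by √(1 − ρ²), which is 0.866 for ρ = 0.5 and 0.714 for ρ = 0.7. Both correlations are assumed.

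| Per arm | Normal | Two-sample t | t, ρ = 0.5 | t, ρ = 0.7 |
|---|---|---|---|---|
| 45 | 0.59 | 0.60 | 0.52 | 0.43 |
| 36 | 0.66 | 0.67 | 0.58 | 0.48 |
| 27 | 0.76 | 0.78 | 0.67 | 0.55 |

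**4. What a smaller margin would need.** With no adjustment, n per arm = 2 × (1.96 + 0.84)²/margin². For an assumed margin of half the planning effect, 0.59/2 = 0.295 SD, this gives 181 analysable per arm. With the planned losses that is 181/(0.80 × 0.75) = 302 recruited per arm. A margin of 0.50 SD would need 63 analysable per arm.

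**5. How often superiority would be inconclusive.** For an assumed true between-arm difference of 0.3 SD, unadjusted two-sided power at 0.05 is 24% with 36 per arm and 19% with 27 per arm. A non-significant result would then occur 76% to 81% of the time.

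**6. The third arm, section by section.**

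| Section | Description |
|---|---|
| Aims and hypotheses | No-treatment control, Phase 2 only |
| Study design | Two arms in Phase 1; in Phase 2 a third, non-treatment and standard-of-care |
| Efficacy analyzes | Waitlist, inside the time factor; group factor has two levels; no phase stated |
| Discussion | Waitlist as a comparator; no phase stated |
| Ethics and dissemination | Larger trial's controls treated once the control phase ends |

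Table 3 has a Phase 2 assessment at week 20. The article does not say when the control phase ends, so it is not clear whether controls are still untreated at that visit.

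**The case against.** The strongest reply is that this is one loose phrase in a Discussion, in a condensed article about a two-phase programme.

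- **It is a question, not a promise.** A reader might infer that the sponsor undertakes to show superiority or non-inferiority. The text says only that the trial will determine whether it holds. Nor does any section say that a non-significant result will be read as non-inferior. That risk is left open by the wording and is not a stated rule. This stands.
- **The size cannot support non-inferiority.** A reader might infer this of the whole trial. It does not follow: the Phase 2 size is deliberately open, and the figures above are for Phase 1, whose stated purpose is feasibility and effect size. This stands.
- **The margin exceeds the whole expected effect.** This is tempting, because 0.60 to 0.78 is larger than 0.59. But 0.59 comes from paired tests and the margin is a between-arm difference, so the scales may differ. The planned analysis uses pre-treatment data, and with ρ = 0.7 every margin falls below 0.59. If Education is truly better by 0.3 SD, the unadjusted margins at 36 and 27 per arm fall to 0.37 and 0.48. The 20% loss is also described as conservative. This stands.
- **The waitlist comparison is impossible.** A reader might infer this from the two-arm Phase 1. The term most plausibly means the Phase 2 arm, whose patients are treated later, and no treatment, usual care and waitlist can describe one arm. What remains is uneven naming and a model sentence that fits neither phase.
- **Similarity would show nothing.** In Phase 2 the untreated arm largely answers this.
- **A margin belongs in the SAP.** Its absence alone is no finding. The conflict between the Discussion and the printed hypotheses, test and sample-size basis is visible without the SAP.

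**Conclusion.** The point holds in limited form. The Discussion allows a conclusion that conflicts with the superiority hypothesis ("more so than the mindfulness group"), and neither the group-by-time test nor the paired sample-size calculation supplies a basis for it. In Phase 1 only fairly wide margins could be excluded: about 0.60 to 0.78 SD unadjusted, or 0.43 to 0.67 SD with an assumed baseline correlation of 0.5 to 0.7. Both ranges assume no true difference, one-sided 0.025 and 80% power. Nothing can be said about Phase 2 until its size is set. Non-inferiority to the untreated arm is not a useful aim in either phase. The waitlist issue is one of consistency: the arm needs one name, a stated phase and a place in the group factor. This should be corrected, because Phase 1 efficacy results are to be published and preliminary efficacy decides whether the larger trial proceeds.

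**What to change.** 1. Delete the non-inferiority parenthesis from the Discussion. State that a non-significant Education versus Mindfulness difference will be reported as inconclusive, with its confidence interval.
2. Alternatively, and for Phase 2 only, specify non-inferiority to Mindfulness in advance: a justified margin on the PMCSMS, the error rate and a between-arm sample size.
3. In Efficacy analyzes, remove the waitlist from the Phase 1 model. Write a separate Phase 2 model whose group factor has three levels.
4. Use one name for the third arm throughout and confine it to Phase 2. Treat the comparison with it as superiority, limited to assessments made before control patients receive treatment.

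Items 1, 3 and 4 are edits to the text and change neither recruitment nor procedures. The cost is that the sponsor gives up a fallback claim. Item 2 costs more, because a margin well below 0.5 SD could need a considerably larger Phase 2.

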## Ethics and dissemination

This trial has already received ethics approval. If preliminary efficacy is observed in Phase 1 of the study, we will conduct a larger scale RCT at the University Health Network (UHN) in which we will provide clinical care through study participation in research. Control arm patients will receive treatment after the control phase. For the larger scale study, subject experts will create presentations that can be delivered by non-experts. We will manualize the entire protocol (comprising a clinician guide, PowerPoint presentations, FAQs), which will be made available to licensed therapists with mental health expertise. For rapid dissemination, the current protocol will be published online early in the study. Feasibility and preliminary efficacy results from the pilot will be submitted for publication as soon as the current pilot is complete. Full-scale results of the planned larger-scale RCT will be published first on bioRxiv (for more rapid sharing of information) and subsequently in peer- reviewed journals. Vehicles for knowledge uptake include: (i) local (Telerehab Centre at UHN; COVID-19 rehab clinic at UHN; CANCOV); Sunnybrook Health Sciences Centre, (ii) study team networks within Canada and abroad (e.g., ECHO COVID; International Neuropsychological Society).

## Ethics statement

This trial received ethical approval from the University Health Network Research Ethics Board (case #21-5038.0), and written informed consent was provided by the participants for participation.
